### 6.3 Identification and Screening (Day 1 or up to 2 working days prior to Day 1)

#### *Figure 1, Step 1*

The Study Champion monitors requests for appointments from potentially eligible patients and will contact them either face-to-face or remotely (via a video/phone call/text). For participants <16 years, a parent/carer will also need to be present, it will not be possible for participants <16 years old to join the trial without parent/carer consent. Patients or parents/carers will be provided a copy of the relevant Participant Information Sheet (PIS) or Booklet (see Table 6) (either as a paper copy or electronic version) and allow them sufficient time to read it. The Study Champion will explain what is involved in the trial and answer any questions. As part of screening, the Study Champion will ask the patient (or parent/carer if the patient is <16 years) if they are happy to answer three short questions giving their views on antibiotics (see Appendix 1, Participant Views questions 1, 2 and 3). It is important these questions are asked before Appointment One since interaction with the Study Clinician could change participant views. The Study Champion will then assign the patient to an appointment with a Study Clinician.

### 6.4 Appointment One (Day 1)

#### *Figure 1, Step 2*

Appointment One will be held either face-to-face or remotely (via a video/phone call). The Study Clinician will assess the patient as per usual clinical care up to (but not including) making the final antibiotic treatment decision which must be deferred until Step 5. The Study Clinician will complete their Study Clinician views (see Appendix 1, Study Clinician Views questions 1 to 5) and then determine eligibility and willingness to take part. The Study Champion or the Study Clinician will take consent (see below) and collect demographic and clinical data. They will also provide the participant or parent/carer with the Trial Diary, either online or in paper format according to participant preference and ask the patient to complete Part A on baseline symptoms and Part B on the EQ-5D. If the patient (or parent/carer if the patient is <16 years) declines to take part in the trial, the reason for this (if provided) will be collected along with brief non-identifiable data including age. Patients who decline will be returned to standard care.

#### 6.4.1 Consent

During Appointment One, the patient will be given the opportunity to understand the nature, significance, implications and risks of the trial in order for them to make an informed decision about whether or not to take part. If the patient wishes to proceed, informed consent will be taken using an e-consent mechanism (where e-consent means the use of electronic methods for seeking, confirming and documenting informed consent and is the preferred option) which will follow Health Research Authority (HRA) and MHRA guidance or if this is not possible paper-based and verbal consent will be considered (see below). The relevant Informed Consent Form (ICF) and Assent Form if required (see Table 6) will be presented in an electronic format and a simple electronic signature will be used to record consent. A copy of the e-consent form will be made available to the participant via email or post.

If verbal consent is taken, it will be documented by the researcher taking consent on the appropriate ICF (and Assent Form if required). The researcher taking consent will record the participant's (or parent's/carer's) responses in each box on the ICF (and Assent Form if required) in the presence of a witness (any member of staff on duty who is not connected with the trial i.e. is not on the Delegation Log) who should also countersign the form. A copy of the completed ICF (and Assent Form if required) will then be sent to the participant (or parent/carer) in the post.

Four copies of the ICF (and Assent Form if required) will be needed: (1) to be provided to the participant along with a copy of the relevant Participant information Sheet; (2) to be filed along with a copy of the relevant Participant Information Sheet in the GP medical records; (3) to be filed in the ISF (4) to be filed in the central TMF.

In addition to completing the consent form, sites should record consent has been given for the trial in the participant's medical records.

To cover the broad age range of participants, a number of different PISs, ICFs, a Children's Booklet, and an Assent Form will be available as shown in Table 6 along with a guide showing which ages these are suitable for. Participants aged 12 - 15 years will need to give their assent plus their parent/carer will need to give consent for the child to be able to take part in the trial. For participants <12 years, their parent/carer will need to give consent for the child to take part. A Summary Leaflet will also be available to supplement the PISs.

**Table 6: Age appropriate versions of information sheets and consent forms**

| Participant Age | Documents to be provided                                                                                                                                 |                                                                                                                                   |
|-----------------|----------------------------------------------------------------------------------------------------------------------------------------------------------|-----------------------------------------------------------------------------------------------------------------------------------|
|                 | PIS/Children's Booklet                                                                                                                                   | ICF/Assent Form                                                                                                                   |
| ≤12 years       | RAPID-TEST Children's Booklet (for the participant)
RAPID-TEST Parent/Carer PIS (for the participant's parent or carer)
RAPID-TEST Summary Leaflet | RAPID-TEST Parent/Carer ICF (for the participant's parent or carer)                                                               |
| 12 – 15 years   | RAPID-TEST PIS 12-15 years (for the participant)
RAPID-TEST Parent/Carer PIS (for the participant's parent or carer)
RAPID-TEST Summary Leaflet    | RAPID-TEST Assent Form 12 – 15 years (for the participant)
RAPID-TEST Parent/Carer ICF (for the participant's parent or carer) |
| ≥16 years       | RAPID-TEST PIS
RAPID-TEST Summary Leaflet                                                                                                             | RAPID-TEST ICF                                                                                                                    |

## 6.5 Swab Collection (Post-Appointment One, Day 1)

### Figure 1, Step 3

The Study Champion or Study Clinician will support the participant to complete their baseline symptoms and EQ-5D in the Trial Diary (Parts A and B) and provide details of how to start filling in the rest of the Trial Diary (Parts C-E).

The Study Champion will also collect post-appointment participant views (see Appendix 1, Participant Views questions 1 to 5). If the participant is <16 years, their parent/carer will complete the post-appointment participant views. If the participant is <16 years, their parent/carer will complete the Trial Diary with, or on behalf of, the participant.

The Study Champion or Study Clinician or another trained member of staff will take a nasal and throat swab from participants who are attending the GP practice. If the participant prefers to take their own swab, or Appointment One is held remotely, the participant (or a member of their household) will be asked to visit the GP practice to collect a trial pack, containing a swab collection kit and instructions on how to take the swab. The swab can be taken and returned at the same visit. If the participants prefers to take the kit home, they will be asked to take and return the swab on the same day as the kit was collected i.e. on Day 1.

Swabs from all participants will be processed according to the Laboratory Manual and while wearing appropriate PPE in line with current guidelines.

## 6.6 Randomisation (Day 1)

### Figure 1, Step 4

Participants will be individually randomised 1:1 to intervention (GP POCTRM test) or control (No GP POCTRM test) using an internet-based randomisation system developed and maintained by Sealed EnvelopeTM. Randomisation will be stratified by age (<16 years vs. ≥16 years) and chronic lung disease (present vs. absent). It will not be possible to blind the allocated randomisation group since the subsequent processes for each group differ.

The Study Champion or Clinician randomises participants and immediately informs (if necessary) the Study Clinician which group the participant has been allocated to.

#### **6.6.1 GP POCTRM Test (Intervention) Group**

A portion of the swab sample from participants in the GP POCTRM test group will be analysed immediately by the Study Champion or Study Clinician using the BioFire® FilmArray® Torch 1 in conjunction with BioFire® RP2.1 *plus* reagent pouches according to the manufacturer's instructions in the GP practice. The time for processing one swab to results being available is approximately 1 hour, assuming the Torch 1 machine is not already in use. The results will indicate presence or absence of 23 upper respiratory microbes: 19 viruses (Influenza A (no subtype detected, H1, H1-2009, H3), Influenza B, Adenovirus, Coronaviruses (HKU1, NL63, 229E, OC43, Mers-CoV, SARS-CoV-2), Human Metapneumovirus, Human Rhinovirus/Enterovirus (not possible to distinguish Human Rhinovirus from Enterovirus due to their genetic similarity), Parainfluenza (types 1, 2, 3, 4) and RSV and four atypical bacteria: Bordetella pertussis, Bordetella parapertussis, Chlamydia pneumoniae and Mycoplasma pneumonia.

The results will be filed in the participant medical notes. The POCTRM does not test for the three typical respiratory bacteria *S. pneumoniae*, *H. influenzae* and *M. catarrhalis* since these are commensally carried in the upper respiratory tract. Hence, Study Clinicians will be advised that the POCTRM result should be used as a guide to clinical decision making, with final responsibility for antibiotic prescribing residing with the Study Clinician. To help with results interpretation, Study Clinicians will be provided with information describing the typical presentation of illnesses caused by the microbes tested as was done in our feasibility study. Further advice will also be available via standard NHS virology services.

If the POCTRM results from a participant's swab sample are reported as equivocal, the original swab sample should be retested once as per the manufacturer's instructions. If the POCTRM results are reported as failed or invalid, the manufacturer's instructions should be followed. If it has not been possible to obtain POCTRM results after following the manufacturer's instructions, this should be recorded in the eCRF. The participant can continue in the trial and the Study Clinician should make a decision about antibiotic prescribing based on the clinical evidence available at that time.

#### **6.6.2 GP POCTRM Test (Intervention) Group and No GP POCTRM Test (Control) Group Central Research Laboratory Analysis**

The remaining swab sample from participants in the GP POCTRM test group and the whole swab sample from participants in the No GP POCTRM test group will be stored at ambient temperature prior to transport. Samples that are not sent on the same day of collection (e.g. missed last collection time), should be stored in the fridge (2-8°C) overnight and sent the next morning. Samples will be transferred within 24 hours to the central research laboratory. Samples will be stored in a linked anonymised format using a combination of trial name, Participant ID, date of birth and date of sample to permit accurate linkage to trial data and the ICF. These samples will be tested for a full array of respiratory viral and bacterial pathogens using a Taqman Low Density PCR array card assay as described in our previous study. The samples will also be tested using the BioFire® RP2.1 *plus* reagent pouches run on the Biofire® Filmarray® Torch 1 system. Once analysis has taken place, any residual sample will be destroyed, unless consent has been provided to include the sample in other research. Where consent has been provided for inclusion of the sample in other research, the sample will be destroyed once all required testing is complete. All samples will be handled according to the Human Tissue Act. Further information relating to the central research laboratory analysis is available in the Laboratory Manual.

### **6.6.3 Study Clinician Views**

#### *Figure 1, Step 5*

Immediately after randomisation and before Appointment Two, the Study Champion will ensure the Study Clinician is aware which group the participant has been allocated to and will provide the POCTRM result for those in the intervention group. The Study Clinician will then complete further data on their views (see Appendix 1, Study Clinician Views questions 1 to 7). Where the participant is in the No GP POCTRM test group, this can be completed immediately after randomisation. Where the participant is in the GP POCTRM test group, the Study Clinician must wait until the POCTRM results are available before completing data on their views.

### **6.7 Appointment Two (Day 1)**

#### *Figure 1, Step 6*

At Appointment Two, the Study Clinician will contact the participant to inform them which randomisation group they were allocated to, what the POCTRM result was (for those in the GP POCTRM test group) and to discuss treatment. Ideally this will be the same Study Clinician who was in contact with the participant at Appointment One.

### **6.8 Post-Appointment Two (Day 1)**

#### *Figure 1, Step 7*

The Study Champion ensures the participant (or parent/carer if the participant is <16 years) completes the post-appointment participant views (see Appendix 1, Participant Views questions 1 to 5). These can be collected face-to-face or remotely (e.g. by phone or text)

### **6.9 Follow-Up**

The Trial Diary will be completed daily by the participant until their symptoms resolve (defined as all symptoms being rated zero for two days in a row) or up to day 28, whichever comes first. The central trial team will contact participants regularly via email, text or phone to support completion of the Trial Diary. Completed paper versions of the Trial Diary should be returned to BTC. Participants will be advised that if their symptoms have not resolved by Day 28, or if they have any concerns before Day 28, they should contact their GP practice for further advice.

Participants (or parent/carer if the participant is <16 years) will be followed-up with a questionnaire at 2 months post-randomisation which will collect beliefs and intention to consult for similar future illnesses (see Appendix 1, Participant Views questions 6 and 7). Up to two reminders will be sent for cases where the questionnaires are not returned. Questionnaires may be completed with the participants over the phone, and the data entered by the central trials team, if required. In addition, data on any further GP consultations for RTIs will be collected from their PCMR at 2- and 6- months after randomisation. For those participants randomised in the later stages of Summer 2, there will be a shorter follow-up period to ensure that all follow-up is completed 2 months after recruitment has finished.

### **6.10 Optional Interviews and DCE Surveys**

During the consent process, participants (or parents/carers if the participant is <16 years) will be asked whether they are interested in being contacted about taking part in an optional Participant Interview and receiving a separate optional Participant DCE Survey. Participants (or parents/carers if the participant is <16 years) can choose to be contacted about the interview and the DCE survey, just one, or neither. This does not affect their ability to take part in the main trial.

Clinicians from each site will be asked whether they are interested in being contacted about taking part in an optional Clinician Interview. In addition, Study Clinicians involved in the trial and other clinicians

recruited through the West of England Clinical Research Network will be invited to complete a Clinician DCE Survey.

See section 7 for further details about the interviews and DCE surveys.

### **6.11 Blinding of Allocated Group**

Post-randomisation, the participants and the Study Clinicians at each site will be informed of the allocated randomisation group since the subsequent processes for each group differ.

A two-stage lock of the trial database will take place; the first lock will include all data from initial screening through to the 2-month PCMR review, and the second lock will include all remaining data which consists of the 6-month PCMR review, safety reporting, change in permissions, and note to files.

The Trial Management Group (TMG) will review unblinded primary outcome and key secondary outcome data after the first data lock. Remaining data will only be reviewed unblinded after all follow up and data queries have been resolved and the second database lock has taken place.

Two statisticians based at BTC will support this trial. The trial statistician will have access to unblinded data while preparing confidential reports for the Data Monitoring Committee (DMC) and will perform all disaggregated analyses according to a pre-specified SAP in addition to attending closed DMC meetings as required.

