## 9.2 Identification of AEs

AEs are expected to occur throughout the course of the trial. Site teams are responsible for recording appropriate AEs for their participants during the trial. The central trial team will contact the sites if additional information is required e.g. to ascertain the nature and severity of an AE. If a participant attends a routine i.e. non-trial related appointment, and an AE is reported, the site team will assess and log this according to the trial recording and reporting procedures as detailed below.

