### **12.1 Trial Management Group (TMG)**

The TMG will have responsibility for the day-to-day management of the trial and will report to the TSC. The TMG will comprise of the CI, all Co-Investigators, Trial Manager and other key BTC trial staff. The TMG will meet on a regular basis with a core working group of staff having frequent progress meetings.

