## 2.6. BLINDING

The participants and the Study Clinicians will not be blinded to the allocation of treatment group. They will be informed the allocation group after randomisation. The BTC trial statistician will be unblinded in-order to report to the Data Monitoring Committee, while the senior statistician will remain blinded. The central trials team will remain blinded, including the chief investigator and trial manager.

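### Safety records stay open until the second database lock, although central staff who may query them will have seen the unblinded main results after the first

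*Combined protocol and SAP*

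**What the plan says.** Protocol 6.11 describes a two-stage lock. On the first stage: "the first lock will include all data from initial screening through to the 2-month PCMR review". On the second: "the second lock will include all remaining data which consists of the 6-month PCMR review, safety reporting", together with changes in permissions and file notes. Between the two, "The Trial Management Group (TMG) will review unblinded primary outcome and key secondary outcome data after the first data lock". The same section then restricts everything else: "Remaining data will only be reviewed unblinded after all follow up and data queries have been resolved", and only once the second lock is in place.

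Protocol 12.1 gives the group's membership: "The TMG will comprise of the CI, all Co-Investigators, Trial Manager and other key BTC trial staff". Protocol 9.2 gives the central team a querying role: "The central trial team will contact the sites if additional information is required e.g. to ascertain the nature and severity of an AE". Protocol 9.5 has that team review the SAE Summary Log regularly. Protocol 9.3 leaves the categorisation of events as serious, expected and related to the principal investigator at each site.

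SAP 2.6 states: "The central trials team will remain blinded, including the chief investigator and trial manager". It gives no point at which that blinding ends. The SAP mentions neither the two-stage lock nor the TMG's review after the first.

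**The concern.** The usual reason for locking data before unblinding is that nobody who knows the result can then influence the data. Here the main outcomes are locked before the TMG is unblinded to them, but the safety records are not. The entries in SAP Supplementary Table 7 (related events, serious events, related serious events, suspected unexpected serious reactions) depend on judgements. Someone who already knows whether prescribing fell and whether symptoms were worse could, without intending to, press some events harder than others or accept a site's description more readily. The trial is meant to show whether antibiotic use can be reduced safely, so the safety table should not be open to that question.

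The two documents also give different accounts of who is blinded. Protocol 6.11 unblinds a group containing the chief investigator and trial manager after the first lock, while SAP 2.6 says without limit that they stay blinded.

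**Working it through.** No formula applies. The check is to set the sections side by side and follow the order of events.

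1. **First lock.** It holds data from screening to the 2-month record review (Protocol 6.11). This includes the primary outcome, the Day 2 to 4 symptom scores and, from the notes to Protocol Table 5, RTI hospital admissions to Day 28. Safety reporting is assigned to the second lock.
2. **Unblinding.** The TMG sees the primary and key secondary outcomes by group (6.11).
3. **Between locks.** Unblinded review of the remaining data waits until queries are resolved, so queries on those data, safety included, may still be open in this interval.
4. **Second lock.** Safety reporting closes, and unblinded review of it follows.

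**Who overlaps between steps 2 and 3.** The TMG includes the chief investigator, trial manager and key trials-centre staff (12.1). SAP 2.6 counts the chief investigator and trial manager within the central trials team. I take this to be the central trial team that queries events (Protocol 9.2), reviews the SAE log (9.5) and receives SUSAR reports, which are also copied to the chief investigator (9.5.1). I found no provision limiting queries between the locks to staff who have not seen the results, or requiring changes made in that interval to be reported.

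**Is there a reason for safety to wait?** Protocol Table 7 defines an adverse event as arising during trial participation, and 6.14 ends participation at the 2-month questionnaire. The onset of reportable events should therefore be essentially complete by the 2-month record review. What may properly remain open is the outcome of an event still being followed, since 9.5 has SAEs followed to resolution or final outcome. That justifies named exceptions. It does not explain holding back the whole safety dataset, and no reason is given for doing so.

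**Sources that close at different times.** An admission within 28 days may appear both in the record review, which is locked first, and in the SAE log, which is locked second. SAP 3.2 itself notes possible overlap between adverse events and diary-reported worsening symptoms, and the diaries are also in the first lock. No step reconciling the SAE log with the admissions is described.

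**How long is the interval?** It is not stated. Protocol 6.9 shortens follow-up for late recruits so that all follow-up finishes 2 months after recruitment ends. The last 2-month reviews and the truncated later follow-up therefore fall due at about the same time, and the gap may be little more than the time needed to collect and clean the remaining records.

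**The case against.** The strongest reply is that the plan already contains the main safeguard. Protocol 6.11 bars unblinded review of the remaining data until the second lock, so the TMG should not see adverse events by group while they can still change. That stands, and it removes the most serious version of the problem. It does not remove knowledge of the main results from those who query events.

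Second, a reader might infer that people who know the results can change or reclassify safety records. The documents do not support that. Site principal investigators classify events (9.3), site principal investigators are not named among the TMG's members, and nothing says that central staff edit the entries. SAEs are also logged, reviewed and reported to the Data Monitoring Committee during the trial, so a later change would depart from what had already been reported. Study Clinicians know the allocation from Day 1, so open-label assessment at sites is probably the larger source of bias, and the lock order does not affect it. What remains is central querying and log review in the knowledge of the results.

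Third, a reader might size the risk from RTI admissions. With 514 / 2 = 257 per group and assumed risks of 0.5% to 2%, that gives 257 × 0.005 = 1.3 to 257 × 0.02 = 5.1 per group. The admission outcome, however, comes from the 2-month record review and is inside the first lock. The documents give no figure for the events left open. Nor do they support saying that the exposure lasts at least as long as the 6-month record review, because of the shortened follow-up in 6.9, or that discrepancies between the sources cannot be corrected: reconciliation before the first lock is not ruled out.

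Fourth, section 2 of the SAP presents itself as a summary of protocol version 3.0 and refers readers elsewhere for other purposes, and its blinding statement may be meant to cover trial conduct only. That is a fair reading, but with two locks the SAP still needs to say which one ends the blinding.

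**Conclusion.** The point holds in a limited form. The stated order leaves AE and SAE records open to central queries after a group that includes the chief investigator, trial manager and key trials-centre staff has seen the unblinded primary and key secondary results. What is exposed is the descriptive content of Supplementary Table 7. SAP 3.2 specifies tabulation only, so no test is at risk, and the primary and key secondary inferences are unaffected. The size of any distortion cannot be calculated, because neither the number of open events nor the interval between locks is given. The planned results paper includes the safety table alongside the efficacy tables, so it would be wrong to infer that efficacy is to be published without safety.

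The conclusion assumes that the central team named in the protocol and in the SAP is the same body, and that queries on safety records do continue between the locks. It is a worthwhile, inexpensive improvement and not a threat to the trial's main findings. The mismatch between SAP 2.6 and Protocol 6.11 needs correcting however the bias risk is judged.

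**What to change.** In Protocol 6.11, put AE and SAE records with onset up to the 2-month review into the first lock, after reconciling the SAE log with the admissions found in the 2-month record review. Reserve the second lock for later-onset events and for outcomes listed as unresolved at the first. Report any change made between the locks to an event with earlier onset.

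If safety data must stay in the second lock, restrict safety queries and SAE log review between the locks to staff who have not seen the results.

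Amend SAP 2.6 to state at which lock blinding ends for the central team, chief investigator and trial manager, consistently with Protocol 6.11.

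The cost is wording in two documents, one reconciliation step and possibly a slightly later first lock. It alters data management only; event definitions and participants' care are unchanged.
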